## Discussion

3

HSPN is a major public health problem and accounts for 78.9% of secondary glomerulopathy in children.^[22]^ Currently, TCM plays a considerable role in symptom and quality of life improvement for HSPN children patients in China and worldwide. In this study, we propose the use of CHM to improve the clinical management of HSPN. A prospective cohort design is employed in the study, and 600 HSPN children patients will be treated as subjects.

To guarantee the quality of the study programs, only patients who meet the inclusion criteria will be recruited. In addition, patients will be excluded if they also suffer from nephritic syndrome, rapidly progressive glomerulonephritis, chronic glomerulonephritis, respiratory diseases, digestive diseases, and liver or mental diseases. The medical therapies associated with these afflictions may interact with the planned interventions, resulting in difficulty in interpreting the clinical results.

It is worth mentioning that we adopted an online clinical research data-capture computer system to collect the data. To minimize the bias and artificial errors of human data management, each patient record will be typed by three researchers and verified before storing. Once stored, the data will be visible to the statisticians and supervisors of this study. They will not be able to modify the data entries. The clinical appraisers and statisticians will be kept unaware of whether a participant belongs to the experimental or the control group. We attempt to establish the chronic disease management programs incorporating information technology (IT) solutions for children with HSPN and explore the effective model for long-term treatment through disease control, psychological intervention, and social support.

The outcomes in the follow-up will include renal events, mortality rate, and adverse events. These outcomes will be easy to assess with only a few questions. The physicians who follow the entire process of the study are familiar with patients and are experienced interviewers. These measures will guarantee the quality of the follow-up. In conclusion, this prospective cohort study will identify whether CHM is helpful for the treatment of HSPN in pediatric patients. The results of this research may generate scientific evidence for further confirmatory studies.

In this trial, we intend to assess the efficacy and advantage of the use of CHM for the treatment of children with HSPN. We hypothesize that CHM will be an effective and safe way to treat HSPN patients and to reduce the recurrence rate.

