#### Primary outcomes

2.5.1

The primary outcomes of this study are remission rate and recurrence rate of HSPN.

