### Data collection

2.8

Both cohorts undergo a 12-week treatment and 12-month follow-up. Case report forms (CRFs) contain a range of information, and these will be completed by the corresponding researchers at each center. The recruited patients will be asked to visit the clinicians 7 times for the assessment of the treatment efficacy during the treatment period (at baseline and in the 2nd, 4th, 6th, 8th, 10th, and 12th weeks after the first treatment). During the follow-up period, patients will be asked to visit once a month. If a patient fails to visit during one of the follow-up observations, the assessor will contact him/her by phone (Table 2). All data collected using paper-based CRFs will be submitted to an online clinical research data-capture computer system developed by the research group (http://59.46.50.9:9889). Only the members from the research team will have access to these data.

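### Recurrence is a primary outcome, but the described follow-up does not name it, lets a phone contact without a urine result stand in for a visit, and leaves its blinding unresolved

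*Protocol article*

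**What the plan says.** Section 2.5.1 states: "The primary outcomes of this study are remission rate and recurrence rate of HSPN". The article's closing statement ties the hypothesis to the same outcome: "We hypothesize that CHM will be an effective and safe way to treat HSPN patients and to reduce the recurrence rate". Urine erythrocytes and urine protein appear in section 2.5.2 as examples of symptom improvement, a secondary outcome.

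On follow-up, section 2.8 says "During the follow-up period, patients will be asked to visit once a month", for 12 months after the 12-week treatment. It adds: "If a patient fails to visit during one of the follow-up observations, the assessor will contact him/her by phone". The Discussion then says "The outcomes in the follow-up will include renal events, mortality rate, and adverse events" and continues "These outcomes will be easy to assess with only a few questions".

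Section 2.9 fills missing data in the final dataset by last observation carried forward (LOCF).

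On blinding, the Discussion says "The clinical appraisers and statisticians will be kept unaware of whether a participant belongs to the experimental or the control group". In the next paragraph it offers as a guarantee of follow-up quality: "The physicians who follow the entire process of the study are familiar with patients and are experienced interviewers".

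**The concern.** Recurrence can be seen only after remission, so the 12-month follow-up carries much of this primary outcome. The one place that lists follow-up outcomes leaves it out and lists renal events and mortality, which section 2.5 does not contain. It also describes a method, asking questions, that cannot supply the urinary findings by which most of the eligible disease is classified.

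Two biases are at stake. A child who relapses without noticeable symptoms while a phone call replaces the visit may be counted as still in remission. That lowers observed recurrence, and lowers it more in whichever cohort attends less. And if the people who judge recurrence know which children take herbal medicine, their judgement may lean with that knowledge while the result is reported as blinded.

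**Working it through.** No figure in the plan can be reproduced for this point. The article gives no recurrence rate, and the sample size in section 2.6 rests on response rates of 53% and 40%. The check therefore sets the passages side by side; the arithmetic at step 4 is illustration only.

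**1. Outcome list.** Section 2.5 has remission, recurrence, symptom improvement and adverse events. The Discussion's follow-up list has renal events, mortality and adverse events. Only adverse events are in both. *Renal events* might be meant to cover relapse, but the term is not defined.

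**2. Method against disease.** Section 2.4.2 admits isolated haematuria, isolated proteinuria, the two combined, and acute glomerulonephritis. Three of these four classes are defined by urinary findings alone. There are two readings of the Discussion:
- If recurrence counts as a renal event, the text says that a few questions suffice for it, which does not fit these classes.
- If it does not, the description of follow-up is silent on a primary outcome.

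Either way the text needs reconciling.

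**3. What happens to a phone-only month.** A call yields no urine value. For a child in remission there are again two routes:
- The month is treated as missing. LOCF then carries the last status, remission, forward.
- The answers given by phone are taken as the status. A relapse visible only in urine is then recorded as absent.

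Both routes end in no recurrence for that month. The final classification is wrong only if the relapse clears before the next urine assessment or the child has no later one. Otherwise the relapse is found late, which distorts its timing but not its occurrence.

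**4. Illustration (all inputs assumed).** Let *p* be true recurrence and *s* the share of relapses never seen because of phone-only follow-up. Observed recurrence = (1 − *s*) × *p*. With no true difference between cohorts, the false gap is *p* × (*s*₂ − *s*₁).

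| *p* | *s*₁ | *s*₂ | Observed rates | False gap |
|---|---|---|---|---|
| 30% | 20% | 20% | 24% and 24% | 0 points |
| 20% | 10% | 30% | 18% and 14% | 4 points |
| 30% | 10% | 30% | 27% and 21% | 6 points |
| 40% | 10% | 30% | 36% and 28% | 8 points |

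Equal losses create no false gap, but they shrink a real one. With true rates of 20% and 30% and *s* = 20% in both cohorts, the observed rates are 0.8 × 20% = 16% and 0.8 × 30% = 24%, so 10 points become 8. With 300 × (1 − 0.20) = 240 per cohort, all counted as at risk of recurrence, and a two-sided test at 0.05, power falls from 71.7% to 59.2%.

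**5. Blinding.** The article speaks of clinical appraisers (Discussion), an assessor who telephones (section 2.8) and physicians who interview (Discussion). It does not say whether these are the same people or who judges recurrence. The cohorts are defined by whether a child takes herbal medicine prescribed individually (section 2.2). A physician who stays with the patients throughout would ordinarily know this.

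**The case against.** The strongest reply is that follow-up is a monthly clinic visit and the phone is only a back-up for a missed one. This stands. A reader might infer that follow-up consists of questions and phone calls and so cannot detect a urinary relapse. The article does not support that. Urine measures are study outcomes, and the symptom score table and visit calendar (Tables 1 and 2) are not reproduced in the text at hand, so urine tests at follow-up visits cannot be ruled out. For the same reason the absence of urinalysis from the safety list in section 2.7 proves nothing.

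A reader might also infer that recurrence has been dropped as an outcome. The Discussion's wording introduces its list as inclusive, not complete, and section 2.5.1 and the hypothesis keep recurrence. What stands is that the list is out of step with them.

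A third tempting inference is that the blinding claim is false. The blinded appraisers could be different people from the interviewing physicians. The article leaves this open, so it is a tension and not a proven contradiction.

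Finally, the article documents no difference in attendance, and cut-offs and detailed coding are commonly left to a full protocol or analysis plan. That is fair. But the phone substitution and the LOCF rule are both stated here, and their combination is a stated choice, not an omitted detail.

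**Conclusion.** The point holds in a limited form. The Discussion's account of follow-up does not match the primary outcome or the largely urinary definition of the disease. Phone contact combined with LOCF gives a definite route by which recurrence may be understated. The bias between cohorts depends on a difference in attendance that the article neither reports nor excludes. Such a difference is possible because the cohorts are formed by treatment received, and its direction is unknown.

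The size cannot be estimated from the article. The gaps of 4 to 8 points above follow from assumed recurrence rates and assumed shares of unseen relapses, and they require those relapses to stay unseen to the end of follow-up. They should not be quoted as expected bias.

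The blinding claim for follow-up is unresolved until the article says who judges recurrence and what they know. The change is worth making because it is cheap and protects a primary outcome.

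**What to change.** - Reconcile the Discussion with sections 2.5.1, 2.5.2 and 2.8: name recurrence as a follow-up outcome, and either add renal events and mortality to section 2.5 with definitions or remove them from the list.
- Derive remission and recurrence from the urine protein and erythrocyte values recorded at visits, by a rule fixed before analysis.
- Code a phone-only month as *not assessed* for recurrence, exempt it from LOCF, and treat recurrence as interval-censored between consecutive urine assessments. Report the number of such months by cohort.
- State who judges recurrence. Limit the blinding claim to laboratory-derived outcomes and coded data unless the interviewing physicians are shown to be unaware of cohort.

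The cost is text changes, a case report form coding rule and a somewhat more complex analysis. This assumes that urine values are already recorded at the monthly visits; the visit calendar should be checked, since the fix costs more if they are not. The downside is that more months count as missing and the blinding claim becomes weaker.
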